### Gases measured by the ingestible sensor

Gas concentrations in the gut are higher than those detected in exhaled breath. To track specific gases/biomarkers produced by endogenous chemical conversions, enzymatic perturbations and the metabolic activity of the intestinal microbiota on their interaction with unabsorbed nutrients, the participants will swallow an ingestible gas-sensing capsule—Atmo Gas Capsule (Atmo Biosciences, Australia)—within 5 min following the intake of the nutritional challenges (lactose and glucose solutions).^88^,^90^ The gas-sensing capsule is a 2 cm long capsule containing miniaturised gas sensors that operate in aerobic and anaerobic conditions, a temperature sensor, a microcontroller, a radio-frequency transmitter and button-sized silver-oxide batteries. The capsule uses a membrane that allows gases to pass through and simultaneously keeps out gastric acid. The gas-sensing capsule will directly sense target gas production within the gut and evaluate the constituents (%) of H_2_, O_2_ and CO_2_, present as the capsule travels through the gastrointestinal tract (GIT). It will use O_2_ concentration to track the capsule’s location and measure gastric, small intestinal and colonic transit time. A temperature sensor will inform participants when the capsule is excreted. Data are collected every 5 min for 72 hours and are transferred from the capsule to an external portable receiver that connects and transmits the data via Bluetooth to a phone application and is transferred to the researchers via an online portal.

#### Bowel sounds measured by wearable sensors

The DigeHealth AG devices (Zurich, Switzerland) are equipped with several features designed to capture comprehensive bowel activity data: a bowel monitoring microphone, an environmental noise microphone, a photoplethysmogram sensor, gyroscopes and accelerometers. Short periods of device removal are allowed for essential hygiene (eg, showering). Participants should refrain from non-essential activities that require the device removal (eg, swimming) during the study monitoring period.

### Metabolites in urine, including lactose-derived metabolites

Lactose and its metabolites, galactose, galactitol and galactonate, will be measured in urine by targeted GC-qTOF, as this method previously demonstrated sensitivity in capturing lactose-derived metabolites,^91^ crucial for the planned mechanistic investigation. Following the published protocol,^91^ samples will be prepared to equal specific gravity to normalise concentration differences. The preparation order and GC-qTOF analysis of samples within and between volunteers will be randomised. Quality control (QC) samples and blanks will aid in data filtering and quality control. Derivatisation will involve mixing 100 µL of each urine sample with 50 µL of an internal standard solution containing isotopically labelled D-fructose and D-xylose. The two-stage derivatisation and subsequent steps will follow the HUSERMET protocol. Urine samples will be analysed on a GC 8890/qTOF 7250, and acquired GC-qTOF chromatograms will undergo untargeted metabolomics analysis for complete molecular characterisation and associations with the breath metabolome.

### Genetic analysis

We will investigate five genetic variants in the minichromosome maintenance complex component 6 (MCM6) upstream of the LCT gene associated with LP. These single-nucleotide polymorphisms (SNPs) are: −13910C>T (rs4988235), −13915T>G (rs41380347), −14010G>C (rs145946881), −22018G>A (rs182549) and −13907C>G (rs41525747). Genomic DNA will be isolated from samples collected from participants using painless buccal swabs for 15–30 s. After collection, test kits will be shipped to the central testing facility for analysis. Samples will be analysed using PCR and allele-specific primer extension to identify the polymorphisms in the MCM6 gene.

#### Metagenomic analysis

Faecal microbiota composition will be evaluated in samples collected by participants using shallow shotgun sequencing. This method, at a resolution as low as 0.5 million sequences per sample, recovers more accurate species-level taxonomic and functional profiles of the human microbiome than the widely applied 16S rRNA gene amplicon (16S) sequencing, which is only accurate to genus level, and is only moderately accurate in predicting functional profiles. The technique thus offers a pragmatic solution to accessing some of the strengths of deep whole-metagenome shotgun sequencing, which provides high taxonomic and functional resolution but is prohibitively expensive for studies with high numbers of samples. Sequencing will be carried out using state-of-the-art Illumina technology and pre-defined data processing pipelines. Collective and specific microbiota composition, alpha and beta diversity and functional differences will be investigated between the three study groups and in relation to baseline diet.

### Dietary analyses

Dietary intake will be assessed by online 24-hour recalls, supported by photo documentation, on four consecutive days (including at least 1 weekend day). Dietary recalls will be conducted using the validated myfood24 platform,^92 93^ adapted for Switzerland by integrating the Swiss Food Composition Database.^94^ All records will be verified and cross-checked by a dietitian. Foods will be grouped according to the Swiss Food Pyramid, with subgroups described by Chatelan *et al*.^95^ Daily intakes for food groups and all macronutrients and micronutrients evaluated will be extracted for further analysis. The dietary intake will be linked with lactose tolerance genotype and phenotypes to provide insights into how different relevant diet features, such as other FODMAPs and dietary fibre, influence lactose metabolism. Further, the analyses of the faecal microbiome will allow dietary data to be integrated with features of the gut microbiome, and both will be associated with the breath metabolome.

### Outcomes

#### Primary endpoints

The primary endpoint is the diagnostic performance of the Lactobreath profiles (the molecular breath profiles) for discriminating different clinical traits associated with LM after lactose intake. The choice of this endpoint allows an objective comparison with the current diagnostic measures used for LI diagnosis. It thus allows the novel test to be benchmarked against the current practice.

#### Secondary endpoints

The secondary endpoints are the clinical and metabolic traits that are associated with LM. These endpoints have been selected to allow a mechanistic understanding of the signals obtained in/as part of the Lactobreath profiles. The secondary endpoints are also important for making the link with existing diagnostic methods used in the assessment of food intolerances.

### Statistical power calculation

Power analyses for human intervention studies conducting metabolomics analyses have been published,^81^ but the applicability of this method still needs to be improved. The Lactobreath project consequently bases the targeted number of participants for each group on previously published evidence by research groups in nutritional metabolomics, including Agroscope.^96^,^98^ Among others, these studies have demonstrated that 12–15 subjects per intervention group are already sufficient to discover, among the thousands of metabolites measured, dozens if not hundreds of postprandial metabolites responding to the intervention differentially with statistical significance after correction for multiple testing. In addition, our recent pilot study on 11 participants for the characterisation of the human postprandial breath metabolome following a nutritional challenge with a standardised meal revealed thousands of features detected using our SESI-MS, including 265 structural candidates for the intervention-related metabolites.^78^ Postprandial metabolomics analysis has also shown its potential to identify distinct human metabotypes, monitor time-resolved metabolic changes underlying a disturbance (eg, stress, starvation, food intake) and regain homeostasis in a group of 70 participants.^99^

### Statistical analysis

#### Primary endpoint

Supervised machine learning algorithms (such as random forest and partial least squares discriminant analysis) will be applied based on Zheng *et al*^100^ and will identify molecular breath profiles that discriminate different clinical traits associated with LM based on the levels of metabolites in the exhaled breath after the intake of lactose. Models will be created to explore separately the breath profiles that are discriminated for each trait of LM, including the response to the LHBT, polymorphisms for LP, lactose-derived metabolites in urine and the GI symptoms of LI taken individually and collectively. To reduce overfitting and deliver reliable estimates of the models, we will apply machine learning with voting, a strategy for classification based on selecting the output with the most classes. Clinical traits will be modelled as either categorical variables, continuous variables or both, where appropriate. This analysis will be conducted first on a subset of 50% of the recruited participants to allow the most predictive metabolites to be identified within the timeframe of the study. The subset will be balanced to represent the three test groups. The same analysis workflow will later be applied to the whole cohort, with 20 participants (stratified for group) removed from all modelling to allow for internal validation of the models. The best profiles (Lactobreath profiles) that associate the breath exhalome with each of the clinical traits of LM will be tested in the 20 remaining participants to assess their validity. Further, to consider the specificity of the Lactobreath profiles for lactose metabolism, the profiles will be evaluated in the participants assigned to the glucose test with additional comparisons between intervention types (glucose vs lactose) across all three participant groups. The molecular profiles with the best performance for predicting LM clinical traits will be retained to determine the identity and quantification of the molecules composing the selected profiles.

The diagnostic performance of the lactose-induced breath profiles identified for the clinical traits will be assessed using the following parameters: sensitivity, specificity, positive predictive value, negative predictive value, the likelihood ratio of a positive test, likelihood ratio of a negative test as described by Beyerlein *et al*^17^ and Jellema *et al*.^81^ For each parameter, the novel breath profiles will be compared with the reference diagnostic tool. The participants are grouped by LHBT and genetic test results as these are commonly used in clinical practice for LI diagnosis and are, therefore, suitable for evaluating the performance of the breath biomarkers. The level of significance will be two-sided (α=0.05). Corrections for multiple testing will be made using the false discovery rate.^101^

Analysis populations: the analysis populations are defined by the criteria used to select the three study groups and the two assigned carbohydrate interventions, resulting in six groups for analysis.

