## Methods and analysis

### Study design

The study design is a randomised, two-arm, double-blinded intervention. The study set-up is a monocentric, national study. The study design allows the discovery of biomarkers that report on LM by comparing the breath response to lactose ingestion in three predefined groups defined by the characteristics of LM. The study began in June 2024, with an expected primary completion by the end of 2025.

The specificity of the candidate biomarkers to lactose exposure will be confirmed by the responses of the biomarker in the control condition (glucose solution). By randomising the participants to lactose or glucose intervention arms, the risk of bias due to unknown confounding factors is reduced. Furthermore, the participants will be blinded to the intervention type received to limit non-metabolic responses to dietary exposure. There is a risk that by using a parallel study design, some variation in the biomarkers that relate to the individual will be introduced; however, for the purpose of diagnostic testing, the biomarkers need to be highly specific and robust to variation between individuals. Consequently, the choice of design could help identify more discriminant biomarkers.

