#### Intervention day

The diet of all selected participants will be restricted for 3 days before the carbohydrate challenge test day to ensure that all FODMAPs are avoided. A standardised diet providing all meals to the participants for 3 days before the test.

On the morning of the test day, the participants will be asked to collect their first test sample, the morning urine and consume 300 mL of water at home. On arrival in the test laboratory (Department of Chemistry and Applied Biosciences at ETHZ), the participants will deliver further samples for baseline measures (figure 2):

Second urine sample.Breath for measure of exhaled H_2_ at times −30 min, −20 min and −10 min.Breath for the measure of exhaled metabolome at times −30 min, −20 min and −10 min.

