### Sample collection

During the baseline period, all participants will collect and send by post stool samples for genomic characterisation of the gut microbiota. Faecal samples will be stored at −80°C. They will be analysed using shallow shotgun sequencing for a mechanistic understanding of the microbial features associated with lactose metabolism.

Breath and urine will be sampled on the intervention day, both before and during the 6 hours following the consumption of the assigned test drink. Breath sampling will be performed using a secondary electrospray ionisation source coupled to a high-resolution mass spectrometry system for direct and real-time detection of VOCs and using an H_2_ breath solid-state sensor for detection of exhaled hydrogen. Standardised breath sampling protocols will be developed for precise measurements of biomarkers of dietary intake and metabolism.

In addition, exhaled breath condensate (EBC) samples will be collected using a glass cold trap cooled to −78°C using a mixture of isopropanol. To collect EBC samples, participants exhale through the spirometry filter and a short-length tube, and their exhaled breath condenses in the cold trap. Blank samples will also be obtained by flushing 2 mL of water through the tubing and freezing it in the cold trap. All EBC samples will be stored at −80°C at the premises of ETHZ until thawed for subsequent analysis. Participants will be provided with the needed breath delivery equipment (ie, mouthpiece) and asked to breathe normally for up to twelve times per sample (this includes baseline measurements). Breath samples will be collected before the intervention and at nine time points following the intervention (15 min, 30 min, 60 min, 90 min, 120 min, 180 min, 240 min, 300 min and 360 min). Participants will be asked to provide four urine samples (two baseline samples before the intervention and two sample pools collected during the intervention (0–180 min and 180–360 min). Samples will be stored at 4°C during the test and before further analysis, all urine samples will be stored at −80°C at ETHZ.

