##### Quantification of breath metabolites

Quantification of selected exhaled breath metabolites of interest is of major importance. Currently, SESI-MS is semi-quantitative and quantification is only possible for the metabolites for which the calibration curves can be obtained. Thus, to quantify detected exhaled breath metabolites, we will use a range of built-in-house or commercial systems for the controllable generation of gaseous standards in a chemical environment simulating human exhaled breath. By generating calibration curves of detected metabolites of interest using reference material, we can provide quantitative information for these specific metabolites. We can already quantify SCFAs in the gas phase (in the range of low ppt to high ppm), which are key bioactive components in the gut produced by dietary components, and the metabolism of lactose by the colon in lactose malabsorbers by colonic fermentation.^86^ This will complement the mechanistic analysis of the H_2_ breath test.

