### Hydrogen breath test

Exhaled breath H_2_ will be measured using a non-invasive hydrogen gas microanalyser (QuinTron BreathTracker Digital Microlyzer, model SC; QuinTron Instrument Company, Milwaukee, Wisconsin, USA). The BreathTracker has a resolution of 1 ppm H_2_ and a linear detection range between 2 and 150 ppm H_2_ with an accuracy of ±2%. It also features a two-step calibration and a purging mode that eliminates cross-interference (inter-subject contamination) and provides a stable internal baseline. The gas analyser will also be calibrated externally using a known-concentration H_2_ compressed gas standard. Breath samples (30 mL each) will be insufflated in the Breath Tracker and will be collected as CO_2_-corrected H_2_, expressed in parts per million (ppm). The maximum increase in breath H_2_ will be calculated by subtracting baseline H_2_ values from the highest H_2_ value post-lactose ingestion based on the BreathTracker readings. An increase of at least 20 ppm hydrogen between any two time points after 30 min in the study will indicate LM.^80 87^

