### Missing data and drop-outs

Missing data will be managed by multiple imputations using the moving average method for the intervention postprandial measurements. Missing data for the baseline measures will be handled by imputing the mean of all baseline measurements available for the participant. Additional subjects will be recruited from the group of participants who complete the home survey, should the number of participants completing the lactose and glucose tests fall below the targeted numbers due to drop-outs.

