## Discussion

The Lactobreath study uses state-of-the-art real-time breath metabolomics, suited for sensitive, non-invasive measurement of breath biomarkers in a controlled nutritional intervention that offers extensive and comprehensive participant characterisation for clinical and metabolic features relevant to lactose metabolism. The holistic approach defined in the Lactobreath study aims to address and explore some of the challenges in the diagnosis of food intolerance by capturing metabolic processes and physiological variables that influence clinical phenotypes. Indeed, the Lactobreath breath profiles focus on assessing clinical symptoms in the context of multiple existing diagnostic tools as well as physiological factors (eg, gut microbiota, GI transit) that are known to influence food intolerance symptoms.

In the clinical field, there is currently a gap in the accurate detection of exhaled breath biomarkers for medical diagnostic tests. The Lactobreath study, with the extensive clinical characterisation of the subjects, aims to support the development of a diagnostic test for LM and LI based on exhaled breath metabolomics, providing a proxy for the subjective GI symptoms experienced by humans. The Lactobreath study will serve as proof of concept to extend the use of breath metabolite profiles to the more holistic topic of the diagnosis of food intolerance and its dietary management with low FODMAP consumption.

Notably, the reproducibility of the findings in different populations will need to be confirmed in a second study. The priority in this study is to confirm the proof of principle that dietary response can be distinguished via breath biomarkers. In this context, selecting participants from a limited population sample is important to control other factors that could confound the findings (eg, ethnic group). Moreover, the specificity of discriminating biomarkers to LM will need to be confirmed in a patient setting with other GI disorders.

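### The primary breath classifiers are stated on post-lactose levels and give the three pre-drink samples no role, so a fasting difference between groups could be reported as a lactose-induced profile

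*Protocol article*

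**What the plan says.** The Primary endpoint paragraph under Statistical analysis states that random forest, partial least squares discriminant analysis or similar methods will find profiles that separate the traits of lactose malabsorption "based on the levels of metabolites in the exhaled breath after the intake of lactose".

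The Intervention day section lists, before the drink, "Breath for the measure of exhaled metabolome at times −30 min, −20 min and −10 min". The Sample collection section adds breath samples "at nine time points following the intervention". No section says that the pre-drink exhalome samples are subtracted, adjusted for or used as model inputs. Two other places do mention baselines:

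- Hydrogen breath test: the maximum rise in H2 "will be calculated by subtracting baseline H_2_ values from the highest H_2_ value post-lactose ingestion".
- Missing data and drop-outs: "Missing data for the baseline measures will be handled by imputing the mean of all baseline measurements available for the participant". The baselines are therefore meant to be used somewhere, but for the breath models the article does not say where.

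The Study design section describes the comparison as one of breath responses to lactose across three predefined groups. The diagnostic-performance paragraph calls the resulting profiles lactose-induced.

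**The concern.** A level measured after the drink is the fasting level plus whatever the drink changed. The groups being separated were selected on lactase genotype and symptoms at screening, so randomisation gives no assurance that their fasting breath is alike. The Study design section itself accepts that with parallel groups "some variation in the biomarkers that relate to the individual will be introduced". A classifier fed post-drink levels can separate groups on what was already present before lactose, and the plan as worded would still call that profile lactose-induced.

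Setting aside 20 participants for internal validation does not expose this, because a real fasting difference between groups is present in them too. What is at stake is attribution: whether a retained profile reflects lactose handling or a standing feature of the people in the group.

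**Working it through.** **Plan's own figure.** There is none to reproduce. The Statistical power calculation section rests on precedent and gives no effect size, SD, power or baseline-to-post correlation. The counts agree: 24+24+72 = 120, 100+20 = 120, 4+4+12 = 20.

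**Group sizes.** The lactose arm is 24−4 = 20, 24−4 = 20 and 72−12 = 60. Groups 1 and 2 (no symptoms) against group 3 (symptoms) is 40 vs 60 in the lactose arm and 8 vs 12 in the glucose arm.

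**How often a pure fasting difference is flagged.** Assume no lactose effect, one feature with SD 1, and a group difference d already present at fasting. Then SE = √(1/n₁ + 1/n₂) and P(flag) = Φ(d/SE − 1.96) + Φ(−d/SE − 1.96), two-sided 0.05, unadjusted. For 40 vs 60, SE = 0.204. For 8 vs 12, SE = 0.456. Apparent AUC = Φ(d/√2).

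| d (SD, assumed) | Flagged, lactose arm 40 vs 60 | Apparent AUC | Seen in glucose arm 8 vs 12 |
|---|---|---|---|
| 0.3 | 31% | 0.58 | 10% |
| 0.5 | 69% | 0.64 | 20% |
| 0.8 | 98% | 0.71 | 42% |
| 1.0 | 99.8% | 0.76 | 59% |

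For the genotype contrast at d = 0.8, the lactose arm is 20 vs 80 (SE 0.25, about 89%) and the glucose arm is 4 vs 16 (SE 0.559, about 30%). If the 20 held-out participants all came from the lactose arm in proportion, 40 vs 60 becomes 32 vs 48 (SE 0.228), and the flag rates at 0.5 and 0.8 SD become about 59% and 94%.

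**The randomised comparison.** Lactose against glucose overall is 100 vs 20: SE = √(1/100 + 1/20) = 0.245, so a 0.8 SD response is detected about 90% of the time. This shows that a feature responds to lactose. Whether the group difference arises from that response is a group-by-arm contrast: SE = √(1/40 + 1/60 + 1/8 + 1/12) = 0.50, so a 0.8 SD contrast is detected about 36% of the time.

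**Precision.** Take one feature, one post-drink sample with variance 1, three baselines, and equal correlation ρ among all samples (assumed).

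- Change from the baseline mean: 4(1−ρ)/3, which equals 1 at ρ = 0.25.
- Baseline-adjusted: 1 − ρ²/[(1+2ρ)/3].

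| ρ | Change | Adjusted |
|---|---|---|
| 0.1 | 1.20 | 0.98 |
| 0.3 | 0.93 | 0.83 |
| 0.5 | 0.67 | 0.63 |
| 0.7 | 0.40 | 0.39 |

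If the baselines correlate 0.9 with each other and 0.5 with the later sample (assumed), the variance of the baseline mean is (1+2×0.9)/3 = 0.933. Adjustment then leaves 1 − 0.25/0.933 = 0.73, and change leaves 1 + 0.933 − 1 = 0.93.

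**What adjustment leaves behind.** Under equal correlation the within-group slope on the baseline mean is 3ρ/(1+2ρ), so a fraction (1−ρ)/(1+2ρ) of a fasting difference between non-randomised groups remains: 0.44 at ρ = 0.3, 0.25 at 0.5 and 0.125 at 0.7. Adjustment alone therefore does not settle attribution.

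**The case against.** The strongest reply is that one clause in a condensed article does not exclude baseline correction. The workflow follows a cited source, the kinetic profile over six hours is part of the plan, and feature pre-processing is often left to the full protocol or analysis plan. This stands: a reader might infer that the plan has decided against using change from baseline, and the article does not say so. What it does is name post-intake levels as the input, with no role for the pre-drink samples, while spelling out the subtraction for H2.

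Second, the glucose arm is a planned check on specificity, and the randomised 100 vs 20 comparison has reasonable power. This stands in part. A purely fasting feature should show no difference between arms. But a feature that rises equally in all groups after lactose, and also differs between groups at fasting, passes that comparison and still discriminates on fasting breath. The article also retains profiles by how well they predict the traits.

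Third, the primary endpoint is diagnostic performance, for which fasting signal is legitimate, and the Study design section argues that markers must withstand variation between people. This is fair. The difficulty is confined to the reading of profiles as responses to lactose.

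Fourth, a reader might infer that the groups must differ through ancestry or dairy avoidance, or that instrument drift must distort levels. The documents do not establish this. Eligibility restricts only residence and language in this respect, but nothing shows that genotype separates ancestry in this sample. Dairy avoidance is conjecture, and all meals are provided for three days beforehand. The instrument is described as semi-quantitative, but it is checked daily with gaseous standards and calibrated at least weekly.

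**Conclusion.** The point holds as a problem of attribution. The stated input is the post-lactose level, three suitable baselines are collected without a stated role, the groups are not randomised, and the result is called lactose-induced. For a fasting difference of 0.5 or 0.8 SD with no lactose effect, the per-feature flag rate is about 69% or 98% in the lactose arm, against about 20% or 42% in the glucose arm. The sizes are assumed, since the article gives none. The rates are for one feature without multiplicity correction; false discovery rate control would lower them but would not remove a real fasting difference.

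A reader might also infer a definite loss of precision, or a factor by which the sample is in effect reduced. The documents do not support that. The gain from adjustment depends on an unknown correlation and shrinks if the baselines resemble each other more than they resemble later samples. Simple change is less precise than the raw level below ρ = 0.25 under equal correlation. The variance ratios describe a comparison of means for one feature at one time point and do not convert to a sample size for a classifier.

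**What to change.** 1. State how the −30, −20 and −10 min samples enter the primary breath models. Adjust each post-drink feature for the participant's mean of the three, with the adjustment fitted within the training data. Use change from baseline only where the feature is detectable at fasting, since a ratio to a near-absent signal is unstable. Do not simply offer the fasting value as another free predictor, because the classifier could then discriminate on it.
2. Run the identical workflow on the pre-drink samples alone as a negative control, and report it beside the primary result.
3. Call a profile lactose-induced only for discrimination beyond that control. Anything else may be reported as predictive of the trait, without attribution to lactose.

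The samples are already scheduled. The cost is analysis wording and one extra model run.
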